**Healthy eating**

1. Do you eat at least 2 portions (200g) of fruit everyday?

□ Always

□ Often

□ Sometimes

□ Never

1. Do you eat at least 2 portions (200g) of vegetables everyday?

□ Always

□ Often

□ Sometimes

□ Never

1. Your diet:

□ Is different everyday

□ Is different only sometimes during a week

□ Is different only during weekend days

□ Is very monotonous

1. Do you drink at least 1 – 1.5 litre mineral water every day?

□ Always

□ Often

□ Sometimes

□ Never

1. Your snacks are based mainly on:

□ Fruit/fruit juice and milk shakes/yoghurt

□ Biscuits/crackers/bread/stick bread

□ Fried patatos/popcorn/krapfen/peanuts/soft drinks

□ Sweets/chocolate/ice cream/cakes

1. Do you eat breakfast?

□ Always

□ Often

□ Sometimes

□ Never

1. How many times do you eat sweets and cakes in 1 week?

□ 1-2

□ 3-4

□ 1 time a day

□ more than 1 time daily

□ 1 time in 10-15 days

□ never

1. How many times do you eat fish in 1 week?

□ 1-2

□ 3-4

□ 1 time a day

□ more than 1 time daily

□ 1 time in 10-15 days

□ never

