3.2 Primary endpoint/outcome

The primary outcomes are categorized as follows: (1) Outcomes directly related to the health status and condition management of the participants (e.g. weight, BMI, HbA1c, blood pressure, waist, generic health status, smoking yes/no, confidence in diabetes management and meal planning, healthy eating) and (2) Outcomes directly related to platform intervention usage:

- Number / Duration of sessions
- Number of users / average sessions per user
- New users
- Monthly Active Users / Weekly Active Users
- Specific actions:
  - # Recipes Viewed, (any indication on favourite content)
  - # Recipe Added / Saved
  - # Meal Plans created
  - # Shopping Actions
    - Carts sent online
    - Meal plans sent to cart
    - In store shopping actions - print, email, sms, app, etc.
    - Number of items shopped / value
- Platform used - app vs web app
- GA audience metrics: Demographics, Geography,
- User Retention
- Top 20 recipes (potentially)
- The average or typical meal plan including health score (potentially)

Additionally, expectations beforehand and satisfaction afterwards will be assessed. Diabetes UK will collect data regarding their traffic on the website and the amount of referrals to the online platform.

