The lead CU researchers will send an invitation email to participants to fill in the first survey (please see Attachment 1) with enclosed Participant Information (PI; please see Attachment_2) and Informed Consent Form (ICF; please see Attachment_3) explaining the project aim, related activities and burden in terms of duration. The email will contain a link to the first survey (hosted by Qualtrics; please see Attachment_4) in which both PI and ICF are embedded. Two automated reminder emails will be send by Qualtrics in cases where participants do not fill in the first survey, one after a week of non-response, and one after two weeks of non-response. All data will be deleted in case there is non-response after the three emails. If participants do not want to be contacted or receive any reminder emails they can email they would like to UNSUBSCRIBE. Each participant will be provided with a unique survey link that recognises each participant by a unique response number only. The end of the first survey will present the option if the participant is (1) willing to participate into a prize draw (using their email address) and (2) willing to participate in follow-up research so selected participants can be approached for the case studies or semi-structured online interviews. After 8 weeks of using the platform, participants will receive an invitation email (please see Attachment_5) to fill in the second survey (please see Attachment_6).

Based on platform usage data (low vs. high engagement) and provided consent at the end of the first survey, participants will be selected for further research activities which consist of case study and semi-structured online interviews. Participants selected for the case study interview will receive an invitation email (please see Attachment_7) with PI (please see Attachment_8) and ICF enclosed. Participants who are willing to participate into the case study interview will sign the ICF (please see Attachment_9) and send it back to the CU lead researcher. Participants who prefer a phone interview can indicate this in an accompanying email. The case study interview outline is presented in Attachment_10.

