**Confidence regarding diabetes management and meal planning**

1. How confident do you currently feel in managing your diabetes?

| 1 – Very unconfident | 2 | 3 | 4 | 5 – Neither confident nor unconfident | 6 | 7 | 8 | 9 | 10 – Very confident |
| --- | --- | --- | --- | --- | --- | --- | --- | --- | --- |
|  |  |  |  |  |  |  |  |  |  |

1. How confident do you currently feel in making healthy food choices?

| 1 – Very unconfident | 2 | 3 | 4 | 5 – Neither confident nor unconfident | 6 | 7 | 8 | 9 | 10 – Very confident |
| --- | --- | --- | --- | --- | --- | --- | --- | --- | --- |
|  |  |  |  |  |  |  |  |  |  |

1. How confident do you currently feel in planning meals efficiently?

| 1 – Very unconfident | 2 | 3 | 4 | 5 – Neither confident nor unconfident | 6 | 7 | 8 | 9 | 10 – Very confident |
| --- | --- | --- | --- | --- | --- | --- | --- | --- | --- |
|  |  |  |  |  |  |  |  |  |  |

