**Confidence regarding diabetes management and meal planning**

1. The platform made me feel more confident in managing my diabetes

| 1 – Very strongly disagree | 2 | 3 | 4 | 5 – Neither agree nor disagree | 6 | 7 | 8 | 9 | 10 – Very strongly agree |
| --- | --- | --- | --- | --- | --- | --- | --- | --- | --- |
|  |  |  |  |  |  |  |  |  |  |

1. After using the platform, I felt more confident in making healthy food choices

| 1 – Very strongly disagree | 2 | 3 | 4 | 5 – Neither agree nor disagree | 6 | 7 | 8 | 9 | 10 – Very strongly agree |
| --- | --- | --- | --- | --- | --- | --- | --- | --- | --- |
|  |  |  |  |  |  |  |  |  |  |

1. After using the platform, I feel more confident planning meals

| 1 – Very unconfident | 2 | 3 | 4 | 5 – Neither confident nor unconfident | 6 | 7 | 8 | 9 | 10 – Very confident |
| --- | --- | --- | --- | --- | --- | --- | --- | --- | --- |
|  |  |  |  |  |  |  |  |  |  |

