**System Usability Scale**

1. How often did you use the platform in the eight week period?

□ never

□ approximately once a month

□ approximately once a week

□ couple of times a week

□ every day

1. How many minutes did you use the platform approximately per session?

_____________ hours _____________ minutes

[figure not shown]

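### The healthy-eating items have no look-back window and, in the second survey only, directly follow statements crediting the platform, so the before-after change in this primary outcome may be diluted, inflated or both

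*Combined protocol and SAP*

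**What the plan says.** Section 3.2 puts "confidence in diabetes management and meal planning, healthy eating" among the primary health outcomes. Sections 1.4 and 8.3.2 compare these outcomes before and after use within one group; there is no control arm. Section 7 sets the follow-up: "After 8 weeks of using the platform, participants will receive an invitation email" for the second survey.

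The eight healthy-eating items are identical in Attachment 4 (first survey) and Attachment 6 (second survey). They are in the habitual present tense, as in "Do you eat at least 2 portions (200g) of fruit everyday", and none names a period to look back over. The sweets and fish items come nearest, for example "How many times do you eat fish in 1 week".

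The lead-in differs. In Attachment 4 the preceding block asks for current confidence, as in "How confident do you currently feel in making healthy food choices", and the expectation statements about the platform come after the diet items. In Attachment 6 the preceding block consists of three statements linking greater confidence to the platform, among them "After using the platform, I felt more confident in making healthy food choices".

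**The concern.** A before-after difference is interpretable only if the same question is asked about clearly separate periods and reached from the same context. Neither condition is secured here.

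Without a look-back window, a respondent at week 8 can reasonably describe a usual diet that reaches back before sign-up, which would shrink a real change. With the changed lead-in, a respondent has just rated whether the platform improved their confidence in food choices and is then asked about food choices, which may encourage consistent answers and so an apparent gain.

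Diet is arguably the outcome a recipe and meal-planning tool is best placed to alter, and sections 1 and 2 say the results will inform a business case for roll-out. Nothing in the plan would detect either effect or separate it from a real change.

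**Working it through.** The plan states no effect size, alpha, power or scoring rule for healthy eating, so there is no figure to reproduce. The check has two parts: a comparison of the surveys, then illustrative arithmetic on stated assumptions.

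**Comparison of the two surveys**

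| Feature | First survey (Attachment 4) | Second survey (Attachment 6) |
| --- | --- | --- |
| Healthy-eating items | eight, habitual present tense | identical |
| Look-back window | none | none |
| Block just before | neutral ratings of current confidence | statements crediting the platform |
| Platform opinion items | after the diet block | directly before it, and again later |

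The weekly wording in the sweets and fish items is a unit of frequency, not a dated period: one answer option is once in 10-15 days. Other measures are anchored in time. General health is rated for the day of completion, the clinical values ask for a date, and platform use has its own window ("How often did you use the platform in the eight week period").

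**Dilution (illustration)**

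Assume that diet changes at sign-up, that the first survey is answered at sign-up, and that at week 8 the respondent averages evenly over the last W weeks. The share of a true change that is recorded is min(8, W)/W:

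- W of 8 weeks or less: 100%
- W = 13: 8/13 = 62%
- W = 26: 8/26 = 31%

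The values of W are assumptions; the documents give none.

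**Shift from the lead-in (illustration)**

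Let b be a shift caused only by the changed context, in SDs of the paired change, with no true change. Assume a two-sided alpha of 0.05 and n = 200 to 300 complete pairs, the range in section 8.1. The false-positive rate is Φ(b√n − 1.96) + Φ(−b√n − 1.96).

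| b | n = 200 | n = 300 |
| --- | --- | --- |
| 0 | 5% | 5% |
| 0.1 | 29% | 41% |
| 0.2 | 81% | 93% |

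The shift that just reaches significance is 1.96/√200 = 0.14 SD or 1.96/√300 = 0.11 SD. The documents give no value for b.

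**Both together**

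With a true improvement of 0.2 SD, W = 16 weeks (8/16 = 50% kept) and b = 0.1, the recorded change is 0.2 × 0.5 + 0.1 = 0.2 SD. The two effects can cancel, or either can dominate.

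**The case against.** A reader might infer that the change in healthy eating *is* diluted and *is* pushed towards benefit. The documents do not support that. Present-tense items can be answered for current diet, in which case nothing is lost at week 8. The lead-in statements are rating scales with a labelled midpoint, so a dissatisfied user could be primed the other way. This objection stands: what is shown is a risk of each effect.

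It would likewise be wrong to quote 31-62% as the expected loss or retention. That range omits the no-dilution case; on the same assumptions it is 31-100%. Most items are ordered or nominal categories with no defined score, so a percentage of the change has no agreed quantity to refer to. This also stands, and the shares serve only as illustration.

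Timing is loose too. The closing note of Attachment 4 counts eight weeks from the first survey, so platform use at follow-up could exceed 8 weeks. This does not by itself remove the dilution, because a late first survey already contains some platform use. With the first survey at week 2 and the second at week 10, a 13-week window keeps 10/13 − 2/13 = 8/13, as before.

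Finally, the project is exploratory, has no hypotheses, lists several primary outcomes, and uses inferential statistics only where possible. Respondents know that the second survey evaluates the platform, whatever the item order. All this lowers the weight of the point. It does not justify leaving a repeated primary measure with a different lead-in at each time, since the difference is avoidable.

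**Conclusion.** The point holds as a risk in both directions. The healthy-eating items lack a look-back window, and only the second survey reaches them through statements crediting the platform. The recorded change may be understated, overstated or, by cancellation, about right; the documents do not allow the net direction or size to be derived. Possible cancellation is no reassurance, because an unknown net bias still blurs the reading of a primary outcome in a study without a control group.

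The illustrative figures rest on assumed even averaging, assumed window lengths, an assumed shift, a conventional alpha and 200-300 complete pairs. This is a modest, correctable weakness in measurement, worth repairing because the repair is nearly free.

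**What to change.** 1. In Attachment 6, move the three platform-confidence statements to after the healthy-eating block, next to the satisfaction items. Both surveys then reach the diet items without platform-crediting statements first.

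2. Head the block with matching 4-week stems. First survey: *Thinking about the 4 weeks before you signed up to the platform*. Second survey: *Thinking about the past 4 weeks*.

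The first stem needs the sign-up anchor because section 7 sends the first survey after sign-up, from email lists passed on weekly, with reminders after one and two weeks. With a plain past-4-weeks stem, a respondent answering two weeks after sign-up would include 2/4 = 50% platform time in the before measure.

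The cost is a reorder and one line of text per survey before launch, with no added items. The downside is a small change to the item wording. The limit is that general demand effects in an uncontrolled evaluation remain and should be stated when the change is reported.

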# 2. RATIONALE

- 1. Aims and hypothesis

This project aims to assess the impact of the platform on important health outcomes across those diagnosed with Diabetes Type 1 or Diabetes 2 (including those who are at risk for developing Type 2 Diabetes). Intervention outcomes will also be examined. There are no specific hypotheses formulated for the current project.

- 1. Justification

This proposed project aims to assess the impact of the platform on important health outcomes and examine intervention outcomes across people with Type 1 or Type 2 Diabetes (or at risk) as referred by Diabetes UK through their website (<https://www.diabetes.org.uk/>). Doing so will allow the West Midland Academic Health and Science Network (WMAHSN) and Diabetes UK to take an informed decision as to whether a business case can be made to support the platform as part of the Diabetes UK ecosystem; and if so, provide supporting information for the business case for further roll-out based on the available evidence and insight gained.

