# 8. STATISTICS AND DATA ANALYSIS

**8.1 Sample size calculation**

The current project consists of platform usage data (collected through Mixpanel), *before* and *after* surveys (anticipated n= 200-300), case studies (n=4) and online semi-structured interviews (n=24). Sample size is not derived statistically but based on the exploratory nature of the project and qualitative case study / interview set-up.

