8.3.2 Primary outcome analysis

Participants will be analysed on health outcomes before and after they used the platform to see if there is an improvement within this group over time. These data will be analysed using IBM SPSS software (version 26) generating descriptive and inferential statistics with reported effect size (if data availability/quality allows). Descriptive data of platform usage (e.g. session frequency, session duration, pages visited, health score for recipes used) will also be provided by the platform developer through Mix panel. These data will be exported into IBM SPSS software (version 26) and will be used to select participants with different engagement levels (low vs. high) for participation in case studies and semi-structured interviews. Where possible descriptive data of platform usage will be related to health outcomes. Results of the case study interviews and semi-structured interviews will be transcribed verbatim and thematically analysed (based on Grounded Theory) resulting in overall key themes. Survey results will be exported to and coded using IBM SPSS software (version 26) and described using descriptive statistics (e.g. frequencies, percentages, medians and means) according to sociodemographic characteristics (e.g. ethnic group, age, digital literacy, educational level, diagnosis and sex).

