**Healthy eating**

1. Do you eat at least 2 portions (200g) of fruit everyday?

□ Always

□ Often

□ Sometimes

□ Never

1. Do you eat at least 2 portions (200g) of vegetables everyday?

□ Always

□ Often

□ Sometimes

□ Never

1. Your diet:

□ Is different everyday

□ Is different only sometimes during a week

□ Is different only during weekend days

□ Is very monotonous

1. Do you drink at least 1 – 1.5 litre mineral water every day?

□ Always

□ Often

□ Sometimes

□ Never

1. Your snacks are based mainly on:

□ Fruit/fruit juice and milk shakes/yoghurt

□ Biscuits/crackers/bread/stick bread

□ Fried patatos/popcorn/krapfen/peanuts/soft drinks

□ Sweets/chocolate/ice cream/cakes

1. Do you eat breakfast?

□ Always

□ Often

□ Sometimes

□ Never

1. How many times do you eat sweets and cakes in 1 week?

□ 1-2

□ 3-4

□ 1 time a day

□ more than 1 time daily

□ 1 time in 10-15 days

□ never

1. How many times do you eat fish in 1 week?

□ 1-2

□ 3-4

□ 1 time a day

□ more than 1 time daily

□ 1 time in 10-15 days

□ never

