**20. Attachment_6: Second Survey**

*Please complete as much information as possible about yourself (or the one you are taking care of) in the survey below.* *All information will be treated in confidence and nothing will be linked to you.*

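### The snack item in both surveys has no answer for people who do not snack, so it cannot record stopping snacking; the mineral-water wording is a lesser companion fault

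*Combined protocol and SAP*

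**What the plan says.** - **Outcome.** Section 3.2 places "confidence in diabetes management and meal planning, healthy eating" in its first group of primary outcomes, those on health status and condition management.
- **Comparison.** Section 8.3.2 states: "Participants will be analysed on health outcomes before and after they used the platform". It promises descriptive statistics, and inferential statistics with effect sizes if the data allow. Neither it nor any other section gives a scoring key, an item direction or a total for the healthy-eating items.
- **Snack item.** Attachments 4 and 6 use the same stem, "Your snacks are based mainly on", and the same four food groups. The list ends at "Sweets/chocolate/ice cream/cakes". No option for none, other, don't know or prefer not to say follows it.
- **Water item.** Both surveys ask "Do you drink at least 1 – 1.5 litre mineral water every day", answered on a four-step frequency scale that ends in never.
- **Blanks.** Attachment 6 opens with "Please complete as much information as possible about yourself", and Attachment 4 opens the same way. Neither says whether items are compulsory. Section 8.6, whose title covers missing or spurious data, deals only with interview and case-study recordings and the withdrawal deadline.
- **Status of the study.** Section 2 says "There are no specific hypotheses formulated for the current project", and Section 8.1 says "Sample size is not derived statistically but based on the exploratory nature of the project".

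**The concern.** A response list that is meant to classify everyone should hold a true answer for everyone. The snack list does not. A person who does not snack at baseline, or who stops during the eight weeks, finds no category that fits. The same is true of someone whose main snack is off the list, such as raw vegetables.

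This matters because the platform exists to support healthy recipes and meal planning (Section 1.1), so giving up snacks is one of the changes it could plausibly bring about. The item that asks about snacks would show that change as a missing value or as a move between snack types. The evaluation is meant to inform a business-case decision (Section 2), and an improvement of this kind would go uncounted on that item.

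The water item raises a related but weaker worry. It names one kind of water, so it may not separate people by how much water they drink.

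**Working it through.** The plan gives no figure to reproduce here. The check compares the items with each other and follows the possible answers through both surveys.

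**1. The eight items side by side.** Six items (fruit, vegetables, water, breakfast, sweets and cakes, fish) include never among their answers. The diet-variety item describes how varied the diet is, so it needs no such option. The snack item is the only one about consuming a food, drink or meal that has no way to say none. Elsewhere the surveys often offer other, don't know or prefer not to say, for example in the sociodemographic and diabetes-related health blocks. The gap looks like an oversight; the documents give no reason for it.

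**2. What the snack item records.**
- *Snacks before and after:* recorded correctly if the main snack is on the list.
- *Snacks before, none after:* the second answer is blank and the pair is lost, or it is a false category and reads as no change or as a switch of snack.
- *None before, snacks after:* the same fault in reverse.
- *None at either time:* two blanks, or false choices that may differ and look like change.

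The before/after table has 4 × 4 = 16 cells, and none of them represents the last three patterns. A blank cannot be told from ordinary non-response, and Section 8.6 gives no rule for it. If Qualtrics were set to force a response, only the false category would remain.

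**3. Size.** Items with no fitting option: 1/8 = 12.5%, in both surveys. The share of respondents affected is not in the documents. Taking 5% to 30% purely as an assumption, and the anticipated 200 to 300 respondents:
- low end: 0.05 × 200 = 10 respondents
- high end: 0.30 × 300 = 90 respondents

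The count at the second survey would be lower if fewer people return it.

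**4. The water item.** A person who drinks only tap water can truthfully answer never.
- *Between people:* ample tap water and very little water of any kind can give the same answer.
- *Within a stable tap-water drinker:* never at both surveys, so no spurious change.
- *Within someone who switches from tap to mineral water:* the answer can move from never to always although total intake is unchanged.
- *Within someone who drinks more tap water:* the answer need not move at all.

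**The case against.** The strongest reply is that little turns on one item. Healthy eating is one of many listed primary outcomes, the study is exploratory without hypotheses, and inferential testing is only where possible. That stands, and it limits the importance of the point.

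A second reply is that other parts of the study could pick up the change. The sweets and cakes item includes never. The second survey asks, with a free-text explanation, whether the platform supported healthy food choices. Interviews may follow up survey answers, and the case-study outline asks about changed eating habits. This stands in part. A reader might infer that stopping snacking cannot be recorded anywhere in the study, and the documents do not support that. But the sweets item covers one food group, the case studies number four, and the rest is free text or interview material. None of it gives a before/after count of people who stopped snacking.

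A third reply is that nobody is shown to be forced into a false answer, since the surveys ask only for as much information as possible. That is fair. The respondent can leave a blank, but the blank has no handling rule and no distinct meaning.

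On water, a reader might infer that tap-water drinkers also have no valid answer, so that 2/8 = 25% of the items fail. That does not hold, because never is literally true for them. Nor is it shown that they would all read the wording so literally. A reader might also infer that either item is mis-scored or given the least favourable score. With no scoring key in the documents, that cannot be said; the answer is at most misclassified or missing on that item.

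**Conclusion.** The point holds for the snack item. In both surveys it has no option for people who do not snack or who mainly eat snacks off the list, and it cannot record a change from snacking to not snacking. This follows from the printed response lists and needs no assumption. Only the number of people affected (10 to 90 in the range above) is assumed. The effect on any healthy-eating total is unknown, because no total is defined.

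For the water item a narrower fault holds: what it measures is unclear. It blurs differences between people and can miss or mimic a change in intake, but it does not create change in people whose habits are stable.

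This is a cheap improvement of modest importance. No conclusion of the study is shown to depend on it.

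**What to change.** - **Snack item, in Attachments 4 and 6 together:** add 'I do not usually eat snacks' and 'Other, please specify'. Report no snacks as its own category in the before/after cross-tabulation.
- **Analysis text:** state in Section 8.3.2 how the eight items will be summarised, and in Section 8.6 how blank items will be handled.
- **Lower priority, also in both surveys:** replace mineral water with 'water (tap or bottled)'.

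The cost is small: edits to two Qualtrics items in each survey. They must be made in both surveys at once, or the before/after comparison is broken. The full snack table grows from 16 to 6 × 6 = 36 cells, which will be sparse at 200 to 300 respondents, so a snacks/no-snacks summary should sit beside it. If the items come from an existing instrument, the new wording would depart from it. The documents cite none: the three references in Section 14 are a usability scale, a prevalence page and a cost study.

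### The sweets and fish items in both surveys have no answer for 5–6 times a week, a gap recoding cannot repair; their out-of-order options also need a stated scoring rule

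*Combined protocol and SAP*

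**What the plan says.** Section 3.2 lists, among the primary health outcomes, "confidence in diabetes management and meal planning, healthy eating". It defines no healthy-eating score. The Healthy eating block has eight items and is the same in the first survey (Attachment 4) and the second (Attachment 6). Two items ask for a weekly count: "How many times do you eat sweets and cakes in 1 week" and "How many times do you eat fish in 1 week". Both offer six answers in this order: 1–2; 3–4; once a day; more than once a day; "1 time in 10-15 days"; never.

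On analysis, section 8.3.2 says: "Participants will be analysed on health outcomes before and after they used the platform". It then says "Survey results will be exported to and coded using IBM SPSS software (version 26"), and that the results will be "described using descriptive statistics (e.g. frequencies, percentages, medians and means"), broken down by sociodemographic characteristics. No section gives codes, an order, a favourable direction or a combination rule for these items. The reference list cites no source for them, so there is no published scoring key to fall back on.

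**The concern.** The platform supplies recipes and meal planning, so eating habits are among the outcomes it is most likely to move. These are the only two healthy-eating items that ask for a weekly count. The answer set jumps from 3–4 a week to 7 a week, which leaves a hole where a modest change from daily intake would land. A wrong answer at baseline cannot be corrected once the survey has gone out.

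The listed order raises a second, lesser question. The two rarest frequencies follow the most frequent one, so position in the list does not track intake. Unless the plan says how the items are scored, two analysts could code the same answers differently.

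**Working it through.** The plan states no figure on this point and has no powered comparison (section 8.1: "Sample size is not derived statistically but based on the exploratory nature of the project"), so there is nothing to reproduce. The check is a count.

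**Inputs.** The six answers and their order come from the Healthy eating blocks of Attachments 4 and 6. Once in 10–15 days equals 7/15 to 7/10, or 0.47 to 0.70 times a week.

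**1. Coverage of weekly counts 0–7.** Never covers 0; 1–2 covers 1 and 2; 3–4 covers 3 and 4; once a day covers 7. Counts 5 and 6 have no answer.

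**2. What the gap does to before/after change.** There are 8 × 8 = 64 before/after pairs of counts 0–7. Of these, 6 × 6 = 36 avoid both 5 and 6, so 64 − 36 = 28 involve at least one. Two of the 28 are stable (5 to 5, 6 to 6) and 26 are real changes. Suppose the respondent answers with the adjacent option, 3–4 (rounding down) or once a day (rounding up):

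| Rounding in the two surveys | Direction recorded correctly | Real change recorded as none | Stable recorded as changed | Reversed |
|---|---|---|---|---|
| Down in both | 18 | 10 | 0 | 0 |
| Up in both | 22 | 6 | 0 | 0 |
| Different in the two surveys | 19 | 6 | 2 | 1 |

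Each row sums to 28. The one reversal is between 5 and 6. With a 5–6 option, only the two moves between 5 and 6 would still read as no change. The hidden changes that the option would prevent are therefore 10 − 2 = 8 (down) or 6 − 2 = 4 (up). With different rounding, all 6 hidden changes lie outside the 5-to-6 moves and would be prevented.

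Example: a fall from 7 to 5 or 6 is recorded as 7 (no change) or as 3–4 (right direction, too large).

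These are counts of possible pairs, not proportions of respondents.

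**3. Listed order against true order.**

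| Answer | Listed position | Rank by frequency |
|---|---|---|
| 1–2 | 1 | 3 |
| 3–4 | 2 | 4 |
| Once a day | 3 | 5 |
| More than once a day | 4 | 6 |
| Once in 10–15 days | 5 | 2 |
| Never | 6 | 1 |

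Six answers give 6 × 5 / 2 = 15 pairs. The 6 pairs among the first four answers agree in order. The 4 × 2 = 8 pairs between those four and the last two are reversed, as is the pair formed by the last two: 8 + 1 = 9 of 15. Kendall's tau is (6 − 9)/15 = −0.20. The squared rank differences sum to 50, so Spearman's rho is 1 − 6 × 50/(6 × 35) = −0.43.

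**4. Recoding.** Coded by true frequency (never = 1 up to more than once a day = 6), 0 of 15 pairs are reversed with no change to the questionnaire. Recoding does not restore counts 5 and 6.

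**5. Number affected.** The share at 5–6 a week is not in the documents. If all of the anticipated 200–300 respondents answered both surveys, each 1% at that level would be 2 to 3 people per item.

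**The case against.** A reader might infer that the answer order itself reverses improvement and worsening. The documents do not support that. The answers carry labels that can be ranked without ambiguity, and section 8.3.2 names coding in SPSS without saying that listed position is the code. Its list of means and medians is a set of examples covering all survey results. It also names frequencies and percentages, which suit categorical items. Reversal is therefore conditional on a coding choice that the plan neither makes nor rules out.

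A reader might also infer that any modest reduction in sweets would be invisible. That too goes further than the text allows. Moves from daily to 3–4, from 3–4 to 1–2, and from 1–2 to once in 10–15 days are all captured. Only respondents at 5–6 a week in at least one survey are affected, in two of eight items. Because both surveys use the same answers, a respondent who rounds the same way twice is never reversed.

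It is fair to add that section 2 states no hypotheses, the project is exploratory, and no specified test or decision rests on these two items. That limits the consequences, but it does not close the gap: for the respondents concerned, no truthful answer exists and no analysis step can supply one.

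The water item in the same block refers only to mineral water. It would be too strong to say that tap-water drinkers must give a low answer, since some will read it as any water. The point stands only as ambiguous wording.

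**Conclusion.** The missing 5–6 answer is a definite defect in both surveys, within a named primary outcome. It forces a false or absent answer and mostly hides or overstates change at that level: 6 to 10 of 28 possible pairs are recorded as no change under consistent rounding. This assumes that respondents choose an adjacent answer. The number of people affected is unknown.

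The listed order and the unstated direction are missing detail in the plan, not a demonstrated error. Scoring by listed position would reverse 9 of 15 pairs, and scoring by true frequency none. This is a small, worthwhile correction, and its value depends on making it before the first survey is sent.

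**What to change.** In both attachments, give the sweets and fish items one ordered, complete set of answers: never / less than once a week / 1–2 / 3–4 / 5–6 times a week / once a day / more than once a day. Both surveys need the same set so that the paired comparison holds.

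Add to section 8.3.2 that each item is coded by true frequency, and that paired movement between ordered categories is reported separately for each item. The investigators should state the favourable direction for each item in advance. The documents give none, and it need not be the same for the two foods.

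As a minor separate edit, change the water item in both surveys to ask about water, tap or bottled.

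The cost is a Qualtrics edit and a line or two of analysis text, with no added question. The small downside is departure from the current item wording. If the first survey has already gone out, only the coding rule can still be applied to those baseline answers.
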